# STATISTICAL METHODS

**10.1 Sample Size Estimation**

Sample size is based primarily on the successful study of RIPC in children (see ref 17) where n=approximately 20 per treatment group. This prior study was amply powered to detect differences in clinical and molecular measures. Notably, post-operative inotrope usage was greatly diminished by RIPC. Based on these inotrope usage results, a power of 0.8, alpha=0.05 and sigma of 3.9 indicates that a sample size of n=20 was required. Injury was deemed to be diminished by RIPC on the basis of reduced troponin I release, thus for a power of 0.8, alpha of 0.05 and a sigma of 3 the sample size required is calculated as n=16. Based on our laboratory’s ability to detect a 20% difference in mitochondrial oxygen consumption in human tissue preparations at least 10 subjects are required to detect this difference (power=0.8, sigma=14.5, alpha=0.05, 2 groups. Similarly, the detection of changes in many mitochondrial proteins measured by proteomic assays, are also quite sensitive ranging between 10-20%. Thus a sample size of n=20 per group will yield ample statistical power.

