**Aim:**

To assess the impact of remote IPC on lactate release, inotrope requirement, and standard clinical cardiopulmonary assessments in response to heart surgery with CPB support.

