**8.1.4. Gel Data Analysis**

Data obtained from the gels will be quantified using the DeCyder version 6.5 software (GE Healthcare). The Differential In-gel analysis (DIA) will be used to optimize spot detection, with the master gel being assigned automatically to the gels with most spots detected. The Biological Variation Analysis (BVA) module will be used for analysis of each sample according to the corresponding age-group. The filtering parameters will then be set to determine the spots that: had a p-value ≤ 0.05 for the t-test employed to test the variation between age-groups and a >1.5 fold change in abundance between the groups.

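### Section 10.1 rests its power conclusion partly on a 10–20% proteomic sensitivity that is not a power calculation and conflicts with the >1.5-fold filter in 8.1.4

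*Protocol*

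**What the plan says.** Section 10.1 gives three calculations and one general statement.

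- Inotrope use: "a power of 0.8, alpha=0.05 and sigma of 3.9 indicates that a sample size of n=20 was required".
- Troponin I: "for a power of 0.8, alpha of 0.05 and a sigma of 3 the sample size required is calculated as n=16".
- Mitochondrial oxygen consumption: at least 10 subjects for a 20% difference, with power 0.8, sigma 14.5, alpha 0.05 and two groups.
- Proteomics: "the detection of changes in many mitochondrial proteins measured by proteomic assays, are also quite sensitive ranging between 10-20" per cent.

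It then concludes: "Thus a sample size of n=20 per group will yield ample statistical power".

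Section 8.1 is the only proteomic profiling workflow described, and it works on plasma. Section 8.1.4 retains spots that "had a p-value ≤ 0.05 for the t-test employed to test the variation between age-groups" and that also show "a >1.5 fold change in abundance between the groups".

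The secondary aim is "To assess the impact of remote IPC on lactate release, inotrope requirement, and standard clinical cardiopulmonary assessments". Troponin I is not named there, in the primary or secondary outcome measures, in the blood allocation (5.1.5) or in the laboratory methods (section 8). It appears only in the background and in 10.1.

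**The concern.** The proteomic sentence is offered as a reason why 20 per group is enough, but it describes what an assay can resolve. Power depends on the spread between patients, the significance level and the group size, and none of these is given for proteins.

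The sentence also conflicts with the protocol's own detection rule. A change of 10–20% lies well below the 1.5-fold threshold, so the screen will almost never report one, however precise the assay.

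The plasma proteomic response is one of the two parts of the primary objective. A reader who trusts 10.1 could take an empty screen as evidence that RIPC causes no protein change of 10–20%, when the screen could hardly have shown one.

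The troponin I sentence is a smaller mismatch: a calculation is cited for a variable that the trial does not list.

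**Working it through.** **Inputs from the protocol.** 20 per group (5.1.1); inotropes sigma 3.9, n=20; troponin I sigma 3, n=16; oxygen consumption difference 20%, sigma 14.5, n≥10 (10.1); filter p ≤ 0.05 and >1.5-fold (8.1.4).

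**Assumptions.** Two-sided tests, since sidedness is not stated. Sigma 14.5 is in percent units. Spot abundance is log-normal, and fold change is the ratio of geometric means. Between-patient CV is 20–50%, because the protocol gives none for proteins. The filter compares RIPC with sham.

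**1. The protocol's own figures.**

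- Oxygen consumption: d = 20/14.5 = 1.379. The two-sample t-test needs 9.3, so 10 per group (power 0.83). The stated 10 reproduces if read as per group. Read as 10 in total (5 per group), power would be 48%.
- Inotropes and troponin I: no difference is stated, so neither n can be tested. If both are per group, the implied differences are 0.909 × 3.9 = 3.5 and 1.024 × 3 = 3.1.

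**2. What 20 per group delivers.** The t-test has 80% power at d = 0.909.

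- Inotropes: 0.909 × 3.9 = 3.5 units.
- Oxygen consumption: 0.909 × 14.5 = 13.2 points. Power for 20% is 0.989.

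**3. The proteomic filter.** On the log scale the between-patient SD is s = √ln(1 + CV²), and the standard error of the observed log ratio is s × √(2/20). At these CVs the fold threshold is the stricter condition: at CV 50%, significance needs a log ratio of about 2.024 × 0.149 = 0.30, against ln 1.5 = 0.405. The pass probability is therefore close to

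P(Z > [ln 1.5 − ln(true ratio)] / SE), plus a negligible opposite tail.

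Example, CV 50% and a true 20% rise: s = √ln 1.25 = 0.472; SE = 0.472 × √0.1 = 0.149; z = (0.405 − 0.182)/0.149 = 1.49; P = 6.8%.

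A simulation of both conditions (100,000 runs per cell) agrees:

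| True change | CV 20% | CV 30% | CV 40% | CV 50% |
|---|---|---|---|---|
| +10%, both conditions | <0.1% | <0.1% | 0.5% | 1.9% |
| +20%, both conditions | <0.1% | 0.8% | 3.3% | 6.8% |
| +20%, p ≤ 0.05 only | 81% | 48% | 31% | 22% |
| 1.5-fold, both conditions | 50% | 50% | 50% | 50% |
| 2-fold, both conditions | 100% | 99.9% | 99% | 97% |

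The 1.5-fold row is 50% by symmetry, because the true value sits on the threshold. Using arithmetic means for the ratio moves the 20% row only slightly, to about 7.5% at CV 50%.

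Without the fold threshold, 80% power at 20 per group needs a CV of about 22% (20/0.909) or less for a 20% change, and about 11% (10/0.909) or less for a 10% change.

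**4. Troponin I.** The largest of the three stated requirements is the inotrope n=20. Removing n=16 leaves 20.

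**The case against.** The strongest reply is that the two statements concern different things: 10.1 speaks of mitochondrial proteins, while 8.1.4 filters plasma spots. Myocardial and lymphocyte proteins go to western blot (8.2.5), which has no fold threshold. This stands in part, and it is why the pass rates hold only for the screen in 8.1. But 10.1 refers to proteomic assays, and 8.1 is the only such workflow. If the 10–20% is not about that screen, the plasma half of the primary objective has no power statement at all.

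A second reply also stands. As written, 8.1.4 compares age groups, and 8.1.5 selects proteins by change from baseline. The pass rates describe the filter as it would work between arms, which the text does not yet say.

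Several stronger readings are tempting but unsupported:

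- *The trial is underpowered or N is wrong.* The one calculation that can be tested reproduces. The proteomic claim is unsupported, which is not the same as a failed calculation.
- *The inotrope n leaves only 80% power with no margin.* This requires n=20 to be per group, which 10.1 does not say. If it were a total, the implied d is 5.17/3.9 = 1.32, and power at 20 per group is 98%.
- *The sample size depends on troponin I.* It does not. Nor does dropping it leave lactate as the only laboratory marker, since creatinine and urea nitrogen are also recorded.
- *A specific multiplicity penalty should be quoted.* The protocol gives no spot count from which to derive one.

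**Conclusion.** The concern holds in limited form. The 10–20% sentence does not support the conclusion of 10.1: it has no variance, alpha or sample size, names a different class of protein from the plasma screen, and conflicts with the screen's threshold.

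Over assumed CVs of 20–50%, a true 20% change is retained at most about 7% of the time and a true 10% change at most about 2%. Only changes well above 1.5-fold are found reliably. The exact percentages depend on the assumed CV and on the definition of the ratio; the conclusion does not, over that range. It does depend on the filter being applied between RIPC and sham.

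The troponin I sentence is an inconsistency between the justification and the outcomes. It has no effect on N.

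**What to change.** In section 10.1:

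- Delete the 10–20% proteomic claim and the unqualified closing conclusion.
- Replace them with what 20 per group provides: 80% power at two-sided alpha 0.05 for a standardised difference of 0.91. That is about 3.5 inotrope units at sigma 3.9, and about 13 points of mitochondrial oxygen consumption if sigma 14.5 is in percent (99% power for 20%).
- State that the proteomic screen, as filtered, reliably finds only changes well above 1.5-fold (a 2-fold change passes 97–100% of the time at CVs of 20–50%), so a null screen is not evidence against changes of 10–20%.
- Delete the troponin I n=16 sentence. Alternatively, list troponin I as a secondary outcome, but only if it is already measured or residual plasma is confirmed: 5.1.5 allots the whole 6.5 ml sample (1.5 + 5).

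In section 8.1.4, reconcile the age-group comparison with RIPC versus sham, and align it with the change-from-baseline selection in 8.1.5.

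The cost is wording, and the stated power will look less favourable. N does not change, and no change of primary endpoint is needed for this point.

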**10.2 Population to be analysed**

The subjects are recruited and consented tetralogy of Fallot patients undergoing first time corrective surgical palliation.

**10.3 Statistical Analysis Plan**

Lab Assay analyses will be performed on coded samples by Drs [name] and [name] and the values then made available for statistical testing when all tests are complete. Statistical analyses will be performed by Drs [name], [name] & [name]. An independent professional statistician experienced in trials will be employed to check and verify the analyses prior to and after breaking the blinding. In addition to two-way ANOVA or unpaired t test, statistical analysis will employ stepwise multivariate regression and analysis of covariance tests in order to determine potential influence of age, gender, bypass time, drugs, body weight and other morphometric and clinical factors.

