**5.1.1 Description**

The hypothesis will be tested in children with tetralogy of Fallot undergoing elective open heart surgery with standard heart arrest and cardiopulmonary bypass. An informed consent will be obtained from all the patients’ parents or guardians. 40 patients will be recruited in to the study within two years. They will be randomized into 2 equal sized groups: Group I control (Sham, n=20) and Group II preconditioning (RIPC, n=20).

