**5.1.5 Blood sampling**

The following 5 blood samples (6.5 ml each) will be taken from the arterial line that is routinely placed in all patients: baseline, immediately after discontinuation of CPB, at 6, 12, and 24 hours following discontinuation of CPB. No additional lines or invasive procedures will be performed apart from those that routinely required for heart surgery. From each sample, 1.5 ml will be used for proteomic assays, and 5 ml for the lymphocyte mitochondrial function assays.

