**8.1.5. Spot Excision and Identification**

Proteins of interest (determined by change from baseline) will be excised robotically using the Ettan Spot-picker (GE Healthcare) and identified by tandem mass spectrometry (MS/MS) on an HPLC-Chip ESI-Trap XCT tandem mass spectrometer or LTQ-FT mass spectrometer. Protein identification will be verified with the use of western blots using specific antibodies.

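### Section 10.3 does not list the child's own baseline value as a covariate for the blood assays, although every child gives one; adding it would be a nearly free gain in precision, mainly for the lymphocyte measures

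*Protocol*

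**What the plan says.** - **Sampling (Protocol 5.1.5).** Arterial blood is drawn at five times: "baseline, immediately after discontinuation of CPB, at 6, 12, and 24 hours following discontinuation of CPB". Each sample is divided between proteomics and lymphocyte mitochondrial function, so both blood assays have a baseline value. Resected myocardium (5.1.4) is obtained once, during surgery, and has none.
- **Group comparison (Protocol 10.3).** "In addition to two-way ANOVA or unpaired t test, statistical analysis will employ stepwise multivariate regression and analysis of covariance tests". The stated purpose of the regression and ANCOVA is to examine age, gender, bypass time, drugs, body weight and an open-ended remainder of morphometric and clinical factors. The two ANOVA factors are not named. Nor is it said whether the t test is run on post-bypass values or on changes.
- **Baseline elsewhere (Protocol 8.1.5).** "Proteins of interest (determined by change from baseline) will be excised robotically". This is the only stated analytical use of baseline, and it concerns which spots to identify.
- **Spot filter (Protocol 8.1.4).** Spots are kept if a t test gives p of 0.05 or less and abundance changes by more than 1.5-fold.
- **Sizing (Protocol 10.1 and 5.1.1).** For mitochondrial oxygen consumption and a 20% difference, "at least 10 subjects are required to detect this difference (power=0.8, sigma=14.5, alpha=0.05, 2 groups". Protein assays are described as "quite sensitive ranging between 10-20" per cent. The arms are "Group I control (Sham, n=20) and Group II preconditioning (RIPC, n=20".

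**The concern.** The blood measures are part of the primary outcome, and the trial has only 40 children, aged one month to 18 years, randomised without stratification. Stable differences between children are therefore a plausible source of noise, and chance imbalance at baseline is possible. A child's own pre-treatment value is the natural way to remove both, and it is already being collected.

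Neither named test makes good use of it. The t test on post-bypass values does not use it at all. A group-by-time ANOVA over five samples would use it as a time level at which no preconditioning effect is expected, so the group main effect averages four informative times with one null time. At stake is precision in the lymphocyte comparisons, and to a smaller extent the proteomic ones.

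**Working it through.** **Inputs**
- From Protocol 10.1: SD 14.5 (read as percentage points), alpha 0.05 (two-sided assumed), power 0.8, difference 20%. It is given for human tissue preparations; using it for blood is an assumption.
- From 5.1.1: n = 20 per group. From 10.1: 10% as the lower end of the range quoted for protein assays.
- Not in the protocol: the correlation r between baseline and post-bypass values. It is assumed, with range 0.3 to 0.7.

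**Step 1: the plan's own figure.** n per group = 2 × (14.5 × 2.80 / 20)² = 8.25, so 9 by the normal approximation. The t-based solution is 9.32, so 10. The stated 10 reproduces, read as per group.

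**Step 2: one post-bypass time, n = 20 per group.** Noncentral t power. Without baseline, noncentrality = (difference / 14.5) × √(20/2), with 38 df. With ANCOVA, divide by √(1 − r²), with 37 df. For a 10% difference this is 2.18 without baseline, and 2.18 / √0.75 = 2.52 at r = 0.5.

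| Difference | No baseline | r = 0.3 | r = 0.5 | r = 0.7 |
|---|---|---|---|---|
| 10% | 56.6% | 60.5% | 68.9% | 84.5% |
| 15% | 89.0% | 91.6% | 95.7% | 99.4% |
| 20% | 98.9% | 99.4% | 99.8% | >99.9% |

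At r = 0.3 the gain is 3.9 points (10%) and 2.6 points (15%). At r = 0 the lost degree of freedom costs 0.1 point (56.6% to 56.5%). Allowing also for expected chance imbalance in baseline (variance × 1 + 1/36), power is 55.4%, a cost of about 1 point.

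**Step 3: change score instead.** The variance factor is 2(1 − r). At 10%, power is 43.5% at r = 0.3 and 56.6% at r = 0.5, so it helps only when r exceeds 0.5.

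**Step 4: average over times, 10% difference, all correlations equal to r.**
- Five times including baseline: effect 0.8 × 10 = 8, variance factor (1 + 4r)/5.
- Four post-bypass times: effect 10, factor (1 + 3r)/4.
- Four post-bypass times adjusted for baseline: effect 10, factor (1 + 3r)/4 − r².

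| | r = 0.3 | r = 0.5 | r = 0.7 |
|---|---|---|---|
| Five times | 72.7% | 59.3% | 49.6% |
| Four post | 86.9% | 76.7% | 67.5% |
| Four post, adjusted | 92.8% | 93.4% | 97.8% |

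Equal correlations are a strong assumption across bypass surgery. With post-to-post 0.5 but baseline-to-post 0.3, the factor is 0.625 − 0.09 = 0.535 and adjusted power is 82.7%, against 76.7% unadjusted. With baseline-to-post 0.2 it is 79.3%.

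**Step 5: proteomic spots.** Under 8.1.2 each gel carries two samples, and its internal standard is made from those two only. On the log scale, a child's standardised value is then about half the difference from its gel partner. If partners are randomised anew at each time, the correlation between times is r/2, so a true 0.5 becomes about 0.25 (a simulation agrees). At 0.25 the 10% case moves from 56.6% to 59.2%. Moreover, a true 10–15% difference lies far below the 1.5-fold filter in 8.1.4, so more power there would rarely change which spots are reported.

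**The case against.** **Silence is not exclusion.** Section 10.3 names ANCOVA, leaves its covariate list open, and does not define the ANOVA factors or the variable tested. A reader might infer that the plan rules baseline out of the group comparison, but no section says so. What stands is narrower: baseline is not listed, and an assay value does not fit naturally among morphometric and clinical factors. If it did, 10.3 would still not make it a fixed term.

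**The effect that is fully specified is already well powered.** At 20% and SD 14.5, power is 98.9% without baseline. This stands. The 10–20% range in 10.1 describes assay sensitivity, not an expected treatment effect, so the 10% and 15% rows are illustrations.

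**Some of the noise may already be removed.** Regression or ANCOVA on age and body weight may absorb part of the between-child variation. This also stands, and the protocol has no figure for how much.

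**The large time-averaged gain is tempting.** A reader might take 77% to 93% as the size of the loss. It depends on equal correlations, and falls to 77% to 83% with a baseline correlation of 0.3. The dilution to 4/5 likewise applies only if the ANOVA is group by time with baseline as a level and the group main effect is the target.

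**Conclusion.** The point holds as an efficiency improvement. A baseline value of each blood assay is collected but not listed as a covariate in 10.3, and an unpaired t test on post-bypass values gives up whatever precision it carries.

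The size cannot be fixed from the protocol. With SD 14.5 carried over to blood and r between 0.3 and 0.7, the single-time gain is about 4 to 28 points at a 10% difference, 3 to 10 points at 15%, and about 1 point or less at 20%. It falls mainly on the lymphocyte mitochondrial measures. It is small for spots, because of the fold-change filter and the two-sample internal standard, and nil for myocardium.

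A reader might conclude that the planned comparison is biased or invalid. It is not: the arms are randomised, and leaving baseline out of a t test on post-bypass values costs precision without making the test wrong.

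**What to change.** 1. In 10.3, make ANCOVA the between-group analysis for each blood measure: post-bypass value as outcome, arm as factor, and the same measure's baseline as a fixed covariate that is always included and not subject to stepwise selection.
2. For all times together, model the four post-bypass values with arm, time, arm by time, and baseline as a covariate. Do not enter baseline as a time level.
3. Align the spot-level t test in 8.1.4 with this, so that the two sections do not prescribe different comparisons.
4. State that the baseline used is a sample drawn before the first cuff inflation. Section 5.1.2 applies the cuff while lines are being placed and 5.1.5 does not give the order; a sample drawn after inflation would not be a clean baseline.
5. Add a simple rule for a missing baseline, such as mean imputation. Myocardial assays stay unadjusted for baseline.

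The cost is wording in two analysis sections, a sentence on sample timing, and one degree of freedom. The plan already calls for these samples and assays.

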**Secondary outcome measures:**

Alveolar-arterial (A-a) oxygen gradient and lung compliance will be obtained as a part of routine clinical assessment. Measures of lung function oxygenation index and alveolar-arterial oxygen gradient at 3, 6, 12, 24 hours post-op. Measurements including mean systemic arterial, and right atrial pressures are made at 3, 6, 12, and 24 hours after aortic cross clamp release. The doses of inotropic, chronotropic, and afterload reducing agents at the time of the cardiac output measurements are recorded. For between-group comparisons, a total inotrope dose score is calculated by adding the doses of dopamine and dobutamine in micrograms per kilogram per minute and assigning an arbitrary equivalent value of 10µg•kg-1•min-1 inotrope for each 0.1µg•kg-1•min-1 epinephrine. Daily post-operative measurements of arterial blood gases, serum glucose, calcium, electrolytes, hematologic parameters, arterial lactate, blood urea nitrogen, and creatinine, the total volume and type of fluid intake, urine output, and chest tube drainage, the total hours of mechanical ventilation and the days in the CICU and the hospital are recorded.

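### Section 10.3 names two-way ANOVA with no within-patient term for outcomes measured 4 or 5 times per patient; run in its ordinary form, its group test would have a type I error of about 15–30% at plausible correlations

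*Protocol*

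**What the plan says.** **Analysis.** Protocol section 10.3, which carries the title of a statistical analysis plan, states: "In addition to two-way ANOVA or unpaired t test, statistical analysis will employ" stepwise regression and analysis of covariance to explore age, sex, bypass time and other factors. It does not name the two factors of the ANOVA, the error term, or which outcome gets which test. No section mentions repeated measures, a patient effect, a mixed model or within-patient correlation.

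**Design.** Section 5.1.1 sets the arms: "Group I control (Sham, n=20) and Group II preconditioning (RIPC, n=20".

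**Serial outcomes.**
- Section 5.1.5 gives the times of the blood samples, which feed the lymphocyte mitochondrial assays: "baseline, immediately after discontinuation of CPB, at 6, 12, and 24 hours following discontinuation of CPB". That is five per patient.
- Section 4.4 gives the lung measures: "Measures of lung function oxygenation index and alveolar-arterial oxygen gradient at 3, 6, 12, 24 hours post-op". The arterial and right atrial pressures also have four times, counted from release of the aortic clamp.

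**Outcomes with one value or their own test.**
- The myocardial specimen is taken on one occasion (section 5.1.4).
- Ventilation hours and lengths of stay are single values (section 4.4).
- The gel proteomics has its own t-test and fold-change filter (section 8.1.4).

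**The concern.** With two arms and no stratification, the natural second factor in a two-way ANOVA is time. That is an inference, since the protocol does not name the factors. Values from one child at successive times are likely to be correlated, and an ordinary two-way ANOVA ignores this.

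Two errors follow, in opposite directions. The arm effect is judged against an error that is too small, so chance differences between 20 and 20 patients are too often declared significant. The arm-by-time effect, which asks whether preconditioning changes the postoperative course, is judged against an error that is too large, so real effects are missed. The lymphocyte assays are part of the primary outcome (signalling in blood and heart muscle), so the problem is not confined to secondary measures.

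**Working it through.** **Inputs from the protocol.** 20 patients per arm (5.1.1); m = 5 blood samples (5.1.5) or m = 4 lung and haemodynamic time points (4.4); nominal level 0.05, as in "a power of 0.8, alpha=0.05 and sigma of 3.9 indicates that a sample size of n=20 was required" (10.1), taken as two-sided. **Input not in the protocol:** the within-patient correlation ρ, shown as a range.

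**The plan's own figure first.** Section 10.1 relies on the laboratory's "ability to detect a 20% difference in mitochondrial oxygen consumption in human tissue preparations" and gives "power=0.8, sigma=14.5, alpha=0.05, 2 groups", with at least 10 subjects. Reading 20% as 20 on the scale of sigma:

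n per group = 2 × (1.960 + 0.842)² × 14.5² / 20² = 8.3, so 9 by the normal formula. The exact t-test gives 9.3, so 10.

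The stated 10 is reproduced, if it is meant per group. This is a two-group calculation with one value per patient, so it offers no repeated-measures model for the serial data. The inotrope and troponin figures cannot be reproduced, because no difference is given for them.

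**Group effect, approximation.** With equal correlation between times, the variance of an arm mean over n patients and m times is σ²[1 + (m − 1)ρ]/(nm). Ordinary ANOVA uses σ²/(nm). The actual level is therefore about

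2 × [1 − Φ(1.96 / √(1 + (m − 1)ρ))].

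- m = 4, ρ = 0.5: the variance ratio is 1 + 3 × 0.5 = 2.5, and the level is 21.5%.
- m = 5, ρ = 0.5: the variance ratio is 1 + 4 × 0.5 = 3.0, and the level is 25.8%.

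**Group-by-time effect.** Its true error variance is σ²(1 − ρ), but the ordinary analysis uses σ². At ρ = 0.5 the F statistic is about half what it should be.

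**Simulation with no true effect** (20,000 trials per setting, equal correlation, nominal 5%):

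| ρ (assumed) | Group, 4 times | Group, 5 times | Group × time, 4 times | Group × time, 5 times |
|---|---|---|---|---|
| 0.1 | 8.6% | 9.3% | 3.2% | 3.3% |
| 0.3 | 15.5% | 18.2% | 1.1% | 0.9% |
| 0.5 | 21.7% | 26.0% | 0.2% | 0.1% |
| 0.7 | 26.6% | 31.5% | 0.0% | 0.0% |
| 0.9 | 31.0% | 36.2% | 0.0% | 0.0% |

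The five-time columns treat baseline as one of the times. If only the four post-bypass samples are analysed, the four-time columns apply.

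With correlation that decays over successive times (lag-one value 0.3 to 0.9), the group-effect level runs from 11% to 30% with four times and from 12% to 35% with five.

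**Check of the remedy.** One mean per patient, compared by an unpaired t test, gave 4.8–5.3% in every setting.

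**Power of the group-by-time test** (illustrative effects, ρ = 0.3 / 0.5 / 0.7):
- A 0.8 SD difference at every time after baseline, five times: ordinary ANOVA 30 / 23 / 14%; within-patient error term 54 / 71 / 92%.
- A difference rising linearly from 0 to 1.5 SD, four times: ordinary ANOVA 87 / 88 / 90%; within-patient error term 95–100%.

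**The case against.** **The method is under-described rather than wrong.** Two-way ANOVA can be run with time as a repeated factor, and a separate analysis plan may say so. This stands in part. A reader might infer that the protocol treats the samples as independent, but it does not say that, so the finding must be conditional. It does name methods for the group comparison, however, and none of them, as written, carries a patient term. An analyst who followed section 10.3 literally could run the ordinary form.

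**The error rate rests on an assumption.** This stands. The documents give no within-patient correlation, so 15–30% cannot be stated without its condition.

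**The unpaired t test is offered as an alternative.** This stands. It is valid at a single time point or on a per-patient summary.

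**Baseline is left out.** A reader might infer this, but the text supports only that baseline is not named as a covariate. Section 10.3 leaves its covariate list open, and section 8.1.5 picks proteins by their change from baseline.

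**An effect on the time course would almost never be found.** A reader might infer this from the near-zero type I error of the group-by-time test. It does not follow: the ordinary analysis still detects a large effect. The supportable statement is a substantial loss of power.

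**An independent statistician will verify the analyses.** This is a safeguard, but verification does not replace naming the model before unblinding.

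**Conclusion.** The point holds in conditional form. Section 10.3 names two-way ANOVA with no within-patient term, although the lymphocyte assays are sampled 5 times per patient and the lung and haemodynamic measures 4 times.

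If that ANOVA is group by time and is run in its ordinary form, the nominal 5% group test has a type I error of about 15–30% for assumed correlations of about 0.3–0.7. Over the wider range of 0.1 to 0.9 it runs from about 9% to 36%. The group-by-time test is conservative and, for the illustrative 0.8 SD effect, has 14–30% power where a correct error term gives 54–92%. These figures assume 20 per arm, complete data, equal variances and, except where stated, equal correlation between times.

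It does not extend to the gel proteomics with its own t-test, the myocardial assays, ventilation hours, lengths of stay, or an unpaired t test at one time point.

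**What to change.** In section 10.3, replace two-way ANOVA for the serial outcomes with one of the following, fixed before unblinding:

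1. A repeated-measures or linear mixed model with arm, time and arm by time, the patient as the repeated unit, and small-sample degrees of freedom (for example Kenward-Roger). Where a baseline value is collected, as for the blood samples, enter it as a covariate and model the post-bypass values.
2. A prespecified per-patient summary, such as the mean of the post-bypass values, compared between arms by ANCOVA with baseline where available.

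State which outcomes this covers, and keep the unpaired comparison for outcomes measured once. The cost is analysis wording only: no added patients, samples or assays, and standard software suffices.
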